### Sensitivity Analysis

In addition to the benchmark analyses described above (3-month and 9-month follow-up examined separately), two types of analyses (ie, complete case analysis—no imputation for missing data—and modified ITT with imputed data) will be implemented using procedures similar to the benchmark analyses (linear and logistic regression models). The robustness of the inferential findings will be assessed by comparing differences in analytical findings across the three types of analyses (ITT with imputed data, complete case analysis, and modified ITT).

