**Conclusions:**

About Us draws on developmental science to create a contextually and developmentally relevant program that addresses motivation and emotional influences in sexual decision-making. The intervention was designed for implementation within SBHCs, an understudied venue for relationship and sexual health promotion interventions. Unfortunately, COVID-19 pandemic restrictions led to school closures, interrupting ongoing programming, and in-person follow-up data collection, which has affected study attrition.

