### Recruitment

#### Power Analyses

For a statistical power of 80%, to detect a 9% difference (effect size: prevalence ratio=0.74, 95% CI 0.60-0.91 equivalent to an odds ratio [OR] of 0.65 or Cohen’s *d*=0.24) in the prevalence of condomless sex at 9 months between intervention and control group participants with an allocation ratio of 3:2, we needed to have a sample size of 508 and 339 subjects in the intervention and control groups, respectively, based on a simple two-tailed proportion difference test at a Type I error of 5%.

We selected a minimum detectable effect of Cohen’s *d*=0.2. The rationale for this selection is two-fold: (1) in our R21 pilot test of a less robust version of the About Us curriculum with a very small (<100) sample, we achieved an estimated effect size of *d*=0.15 for our unprotected sex outcome, and (2) in a meta-analysis of group-based pregnancy or STI interventions, the average effect size across multiple studies was OR 0.70, which corresponds to a small Cohen’s *d*=0.19 [26,27].

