### Handling Missing Data

Our general approach to missing data will involve taking advantage of all observed information while not exaggerating the precision of findings based on incomplete data [41,42].

All variables described for our final regression models will be used in our imputation procedures. That is, outcome measures (at 3-month and 9-month follow-up analyzed separately), treatment condition, baseline outcome variables, strata variables (sex and number of screening experience factors present), sociodemographic characteristics (age, race, and ethnicity), the time elapsed between baseline and follow-up survey (at 3-month or 9-month follow-up), and school. The treatment and control group participant data will be imputed separately [43].

Multivariate imputation by chained equations [44] methods using PROC MI and MIANALYZE procedures in SAS will be used to create multiple imputations (replacement values) for multivariate missing data (eg, continuous, binary, unordered categorical, and ordered categorical data) based on a fully conditional specification [45], where each incomplete variable is imputed by a separate model [46]. All missingness (nonresponse, program attrition, or study loss to follow-up) will be treated the same way for our benchmark analysis. Additional analyses (see Sensitivity Analysis) will be explored where reasons for program attrition are accounted for in the generation of imputed covariate and outcome values. All variables (ie, outcome and baseline characteristics) described in the above analysis models will be used for the imputation procedures. The number of data sets to be imputed will be determined using the quadratic rule recommended by von Hippel [47]. In addition to the baseline value of the outcome of interest, age, race and ethnicity, the sex assigned at birth, and the number of screening experience factors (1 or 2; ie, adolescents had either exposure to violence or a prior or current experience with a romantic relationship or both), and time (days) between baseline and 3-month or 9-month follow-up will be included in our final analysis models (ie, linear and logistic regression).

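### Agreement among the three planned analyses cannot exclude bias from loss to follow-up that is related to the unobserved 9-month outcome and differs between arms

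*Protocol article*

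**What the plan says.** Under Generalities of Statistical Analysis Methods, the benchmark data set is everyone randomized, with missing outcomes and covariates imputed. Modified ITT is restricted to those with baseline outcome measures and at least one follow-up. Handling Missing Data specifies chained-equation imputation in SAS, run separately by arm, using the variables of the final regression models, with 3-month and 9-month outcomes handled separately. It adds: "All missingness (nonresponse, program attrition, or study loss to follow-up) will be treated the same way for our benchmark analysis".

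Sensitivity Analysis then names complete case and modified ITT with imputed data as the two further analyses and sets the criterion: "The robustness of the inferential findings will be assessed by comparing differences in analytical findings across the three types of analyses".

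The Abstract's Conclusions say that COVID-19 closures had the effect of "interrupting ongoing programming, and in-person follow-up data collection, which has affected study attrition". Limitations adds incomplete contact details and school transfers. No attrition rate is given; the 400 of 533 under Assessment of Baseline Equivalence is a worked example.

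**The concern.** A sensitivity analysis informs about missing data only if it relaxes the assumption that the main analysis makes. Here the benchmark and both comparators share that assumption. If loss depended on the unseen outcome differently in the two arms, all three would move together, and close agreement would be reported as robustness. Because the article states the criterion itself, this is not merely a detail left to an analysis plan that is not shown. What is at stake is how a positive (or null) 9-month result is described, in a trial whose authors name attrition as a consequence of the pandemic.

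**Working it through.** **1. What each analysis assumes.**

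- Complete case logistic regression: responding is unrelated to the 9-month outcome, given arm and the model covariates.
- Imputed ITT: imputation from essentially those same variables, by arm, with no shift for non-responders. In practice this is the same condition.
- Modified ITT: the same kind of imputation on a subset.

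**2. The plan's own effect.** Power Analyses gives "For a statistical power of 80%, to detect a 9% difference" and "prevalence ratio=0.74, 95% CI 0.60-0.91 equivalent to an odds ratio [OR] of 0.65". So control prevalence = 0.09/(1 − 0.74) = 0.346, intervention = 0.256, and OR = (0.256/0.744)/(0.346/0.654) = 0.65, as stated. With k = 1.5 and pooled prevalence (0.346 + 1.5 × 0.256)/2.5 = 0.292:

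n(control) = [1.96 × √(1.667 × 0.292 × 0.708) + 0.842 × √(0.346 × 0.654 + 0.256 × 0.744/1.5)]² / 0.09² = 337, and 506 for intervention. The stated 508 and 339 are reproduced within 1%. No figure in the plan is wrong on this point; 0.65 serves as a yardstick below.

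**3. Size of the possible bias (assumptions, since the article gives no rates).** No true effect, prevalence 30% in both arms, 30% missing in About Us and 25% in control. Among responders, before covariate adjustment:

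OR(responders) = true OR × [P(respond | condomless)/P(respond | not)] in About Us ÷ the same ratio in control.

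Response probabilities are solved so that the overall missing fraction is as assumed and the odds of being missing are multiplied by the tie in those with the outcome.

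| Tie | About Us ratio | Control ratio if tied | OR, About Us only | OR, both arms |
|---|---|---|---|---|
| 2 | 0.594/0.745 = 0.797 | 0.654/0.791 = 0.827 | 0.80 | 0.797/0.827 = 0.96 |
| 3 | 0.531/0.773 = 0.687 | 0.596/0.816 = 0.731 | 0.69 | 0.687/0.731 = 0.94 |

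**4. Do the three analyses separate?** Simulated trials with 316 and 217 participants, covariate-adjusted logistic models and arm-specific imputation:

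- Tie confined to About Us: all three analyses give an OR of about 0.79 at tie 2 and about 0.67 at tie 3 (0.65 to 0.68 across runs with slightly different settings). The null is rejected in about 14–19% and 36–41% of trials, instead of 5%.
- Separate setting: control prevalence near 35%; About Us retention 60% with the outcome and 83% without; control 75%. All three give 0.735, with 26–27% rejection. The full data give 1.01 and 5%.
- Missing at random given the baseline outcome: all three give 1.01, with 3.5–4.3% rejection.
- Retention of 60% and 83% by outcome in both arms: all three give about 0.99.

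The mean gap between the largest and smallest of the three log ORs is 0.03 to 0.04 with or without bias, against a standard error of about 0.24. Agreement therefore carries no information about this bias.

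**5. Would a delta shift reveal it?** At tie 2 in About Us, responder prevalence is 25.5%. Doubling the odds for non-responders gives 40.6%, and 0.70 × 0.2546 + 0.30 × 0.4059 = 0.300, so the OR returns to 1.0.

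Applied to the design effect (observed OR 0.65), with shifts of 1.5, 2 and 3 in About Us only, the OR becomes:

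- 85% retention: 0.69, 0.73, 0.79
- 75% retention: 0.73, 0.79, 0.89
- 65% retention: 0.76, 0.85, 0.99

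**The case against.** The strongest reply is that the article plans more than three analyses and that a condensed article may leave detail elsewhere. Handling Missing Data says that imputation using reasons for program attrition will be explored, and Generalities promises modified ITT under different missing-data conditions. Both are real statements of intent. Neither is developed in the article, the first concerns leaving the program rather than missing the survey, and neither is part of the stated criterion.

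The exploratory mixed model uses all time points. If loss follows 3-month behaviour, 3-month data can help: in one such simulation with a true OR of 1, complete case gave 0.91 and imputation using 3-month data gave 1.01. If loss follows the 9-month outcome itself, adding the 3-month outcome changed little (0.81 and 0.69 in all three analyses). The completer baseline comparisons see only observed variables. None of these tests loss driven by the unseen 9-month outcome.

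Three stronger readings are tempting, and the documents do not support them.

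- A reader might infer that the three estimates must coincide. They need not: imputation is by arm, fills missing covariates, and its explicit list omits cohort, which is in the analysis model. With effect heterogeneity, complete case gave 0.73 and imputation 0.70 (full data 0.69), a small but systematic gap.
- A reader might infer that the larger biases are expected. They need outcome-related loss confined to, or much stronger in, one arm. The causes that the authors name (closures, contact details, transfers) are not arm-specific.
- A reader might infer more loss in About Us from its session contact and US $30 payment. That payment was for attending sessions, survey incentives went to both arms, and extra contact would more naturally improve retention there.

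**Conclusion.** The point holds in a limited form. Agreement among imputed ITT, complete case and modified ITT cannot exclude bias from arm-differential loss related to the unobserved 9-month outcome, because all three rest on practically the same missing-at-random condition. Under the assumed 30%/25% attrition, 30% prevalence and no true effect, a tie of 2 to 3 in About Us alone gives an OR of about 0.79 to 0.67 in every analysis, the latter close to the design effect of 0.65. A similar tie in both arms gives about 0.96 to 0.94. The article does not show that arm-differential loss occurred, and it does not rule it out. The benchmark analysis can stand; it is the robustness criterion that needs changing.

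**What to change.** For the 9-month primary outcome, add a prespecified delta-adjusted (pattern-mixture) version of the planned PROC MI imputation. Shift the log-odds of imputed outcomes separately in each arm, over a grid that includes equal shifts in both arms (for example, odds ratios of 1 to 3 for missing versus observed), and report where the conclusion changes. Base any statement on robustness to attrition on that result. Keep the three-way comparison, but present it only as a check on the analysis set and implementation.

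The cost is a few lines of SAS and one table, with no new data. The downside is that the range of shifts is a judgement and the result may look less robust than hoped.

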## Results

Baseline data collection commenced in February 2018 and was completed in March 2020, yielding 5 cohorts and 533 study participants, with 316 assigned to the intervention group and 217 assigned to the control group. Though the project team anticipated an additional semester of implementation in the fall of 2020, the COVID-19 pandemic and subsequent school closures interfered with the scheduling of additional programming. We continued with online data collection and anticipate the completion of follow-up data collection by May 2021.

## Discussion

### Support for the Intervention

Most of the existing EBPs yield relatively short-term gains [48] and were developed using normative decision-making models [49]. These models describe decision-making as a deliberate and analytic process and are useful for predicting behaviors that are typically unemotional [50]; the utility of these models is limited for sexual behaviors, which are inherently emotional. Findings stemming from developmental neuroscience experts suggest that changes in relational, emotional, and social processing play a critical role in influencing adolescent behavior, highlighting the potential of integrating emotionally relevant learning strategies into sexual health programs; by doing so, the content becomes more meaningful and relevant to adolescents, and better supports the development of decision-making skills [51]. Further, most existing interventions are inherently cognitive, teaching adolescents how to refuse unwanted or unprotected sexual intercourse, but do not address the circumstances or situations under which adolescents might be willing to engage in certain sexual behaviors [51]. About Us draws on this body of research to create a more contextually and developmentally relevant program that addresses motivation and emotional influences in sexual decision-making.

The lack of student interactivity is a major pedagogical issue facing learning environments today [52]. EBPs for teen pregnancy and STI prevention share similar interactive instructional strategies (eg, mini-lectures, games, role-playing, and simulations); however, other strategies could extend the program’s impact. Strategies include storytelling and the use of blended learning. Stories have been recognized for centuries as a powerful tool for organizing and transmitting information [53]. They are one way to pique students’ curiosity and build interest while framing new concepts, illustrating consequences, modeling skills, and providing context. Neuroscience supports the use of stories as anchors of information assisting in the learning process [54]. In addition, educators now emphasize the importance of blended learning, which incorporates the use of new online technologies in face-to-face settings to engage students in active and interactive learning [55]. The potential of using technology in changing sexual behaviors is highlighted in research with computer-based or blended learning programs [56,57].

Further, technology provides young people with opportunities to gain virtual experiences related to relationships. Some research suggests there is an association between emotional experience gained in virtual environments with emotional experiences lived in real-life contexts, which can provide a safe and low-risk venue for emotional learning [58]. We draw on both of these strategies in this project.

### Limitations

This study is not without limitations. The COVID-19 global pandemic severely impacted this project. As a result, policies enacted by state and local governments, by school sites participating in About Us, and by the research institutions conducting the evaluation were implemented to protect as many people as possible from the virus. This included suspending in-person intervention delivery, recruitment, and data collection and necessitated the transition to online-only follow-up survey administrations beginning in March 2020. These changes reduced the number of students recruited and prevented those who had already been recruited from receiving the intervention.

Implementation of the intervention was also impacted by instances of turnover within schools and health centers, which sometimes confused all stakeholders. For example, new administrators frequently had no knowledge of the research study because it had not been communicated to them by the outgoing administrators. Similarly, new health center staff were often overwhelmed by “inheriting” this new program from a predecessor, thus slowing the pace of required implementation and evaluation activities. These instances of turnover combined with the challenges of scheduling intervention delivery to occur during the already limited regular school day or after school resulted in lower enrollment in the study.

Another limitation was the incompleteness of the contact information provided by adolescents participating in the study. For example, in some instances, adolescents either initially provided incorrect information or did not provide updated information for study team members to use for follow-up contact attempts. This reduced our follow-up survey response rate and resulted in participants being lost to follow-up. When possible, study team members worked with SBHC staff to reach students with outdated or incorrect contact information and encourage them to participate in scheduled survey administration.

The study was also impacted by a lower-than-expected number of returned consent forms, which resulted in lower-than-expected enrollment. SBHC staff utilized various methods for distributing the consent forms (eg, individually to each student during screening visits or in a welcome packet for parents at the beginning of school term), but the collection of consent forms may have been negatively impacted by lack of follow-up with adolescents about returning the forms to the SBHC. While our study team employed methods previously shown to be associated with improved consent form return in youth samples (eg, providing incentives for consent form return or utilizing school staff for consent form collection) [59,60], additional approaches such as greater engagement with parents or using an opt-out versus an opt-in approach where appropriate may improve consent form return rates.

In some cases, adolescents transferred to different school sites that were not involved in the study. In these instances, we could not rely on SBHC staff to reach out to adolescents if their contact information was incorrect or incomplete, and they were lost to follow-up.

## Appendix

Multimedia Appendix 1 Supplementary tables.

## Abbreviations

BAU: business as usual
CSHA: California School-Based Health Alliance
EBP: evidence-based practice
EDC: evaluation data collector
GLMM: generalized linear mixed model
ITT: intent-to-treat
LS: least squares
OR: odds ratio
PREIS: Personal Responsibility Education Innovative Strategies
PYD: positive youth development
RCT: randomized controlled trial
SBHC: school-based health center
STI: sexually transmitted infections
